### Outcomes {12}

The primary endpoint of the study is the S-NAB adapted to German language [45, 46]. As a comprehensive test battery for neuropsychological assessment, the S-NAB is primarily used in clinical neuropsychology with adults aged 18 and older. The S-NAB combines 14 individual neuropsychological tasks and thus offers the possibility of gaining a diagnostic overview in a short time frame. The functional areas of attention, language, memory, perception, and executive functions are examined with at least two tasks each. Due to its short duration, the S-NAB module is well-suited for patients with limited resilience. Compared to other neuropsychological screenings, the tasks of the S-NAB are challenging enough to detect mild to moderate cognitive impairment [47]. Furthermore, the S-NAB is available in two parallel versions, which is a necessity for the pre-post design of the current study. The S-NAB offers norm scores covering the entire adult age range based on a representative sample from Germany. Additionally, the S-NAB has a mean score of 100 with a standard deviation of 15.

Several important psychosocial and health-related aspects were selected as secondary endpoints. Therefore, in the current study, the following constructs were recorded: psychological well-being, self-efficacy, depressive symptoms, and anxiety symptoms.

The Hamburg Modules for the Assessment of General Aspects of Psychosocial Health for Therapeutic Practice (HEALTH-49) is a self-report instrument for the multidimensional assessment of psychosocial health [48]. This instrument takes into account psychosocial aspects in therapy planning and diagnostics, as well as in quality assurance and the evaluation of psychotherapeutic and medical treatments in general. For the current study, the two modules Psychological Well-Being (5 questions) and Self-Efficacy (5 questions) of the HEALTH-49 were selected. Each module is rated on a Likert-type scale ranging from zero to four, with total scores that are averaged. Additionally, lower scores on both subscales are indicative of elevated levels of self-efficacy and general well-being.

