The Hospital Anxiety and Depression Scale—German Version (HADS-D) is a medical psychological questionnaire and is used to assess anxiety and depressive symptoms in patients with physical illnesses or physical complaints [49–51]. The extent of anxious and depressive symptoms during the past week is assessed by means of self-report, which is recorded on two Likert-type subscales with seven items each that range from zero to three. Higher total scores on the subscales indicate higher levels of anxiety or depressive symptoms. The cumulative score of the two subscales provides a measure of general psychological impairment.

Especially in the context of neurological diseases, a significant measure of quality of life involves the subjective impairment resulting from the disease’s impact on cognitive failures in daily life. The Cognitive Failures Questionnaire—German Version (CFQ-D [52]) is a self-assessment questionnaire consisting of 32 Likert-type items. It evaluates the frequency of committed everyday errors in the past year across the domains of perception, memory, and action regulation [53, 54]. The items are scored on a scale from zero to four. By summing up all the item scores, the total score is derived, which serves as a measure of an individual’s inclination to make everyday errors. Higher total scores indicate a higher subjective probability of encountering everyday mistakes and cognitive lapses.

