Health literacy and patient sovereignty are potential influencing factors on patient health, as higher competence and sovereignty in this area is associated with both higher treatment adherence and better preventive health behaviors [55]. Measurement of this aspect is crucial, serving as both a control variable to ensure comparability between the intervention and control groups, and as a means to detect potential positive effects of the intervention on this aspect. The Health Literacy Questionnaire—German Version (HLQ-G) [56, 57] was selected as the measurement instrument. The questionnaire comprises 44 questions distributed across nine domains, with each domain containing 4 to 6 questions. The domains capture (1) feeling understood and supported by health care providers, (2) having enough information to manage one’s own health, (3) actively doing something for one’s own health, (4) social support for one’s health, (5) evaluating health information, (6) ability to actively engage with health care providers, (7) navigating the healthcare system, (8) ability to find good health information, and (9) understand health information well enough to apply it. For the first five subscales, the scores range from 1 to 4, while for scale six to nine, the scores range from 1 to 5. Higher scores reflect higher health literacy. To obtain scores for each domain, the response to the questions are summed and averaged.

In order to analyze the usability of the NeuroNation MED app, the System Usability Scale (SUS) is used [58]. This is a widely used questionnaire developed to assess the usability of a system, product, or service. It consists of 10 items on a 5-point Likert scale that measures the user’s perception of various aspects of usability, such as ease of use, learnability, efficiency, and satisfaction. The SUS provides a standardized and reliable method to evaluate and compare the usability of different systems. The SUS score ranges from 0 to 100 and can be interpreted in many ways, e.g., by percentiles, grades, acceptability, adjectives, or the Net Promoter Score. The raw SUS values can be converted into percentile ranks. The average value at the 50th percentile is 68.

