### Sample size {14}

The assumed effect size is based on results of previous studies using the cognitive training program “NeuroNation BT” [69] and comparable digital cognitive training applications [25, 26, 36, 70]. A calculation by means of a *t*-test for independent samples was used as the basis for the sample size calculation within the trial described here. With an allocation ratio of 2:1, if 164 subjects are included in the IG and 82 subjects are included in the control group, differences with an effect size of 0.39 or greater can be shown (a priori power analysis, Wilcoxon-Mann–Whitney test (two groups), power = 80%, two tails significance level *α* = 0.05). This resulted in the total sample size of 246. We expect a drop-out rate of approximately 15% [71], which results in a sample size to be recruited of *N* = 286. This sample size calculation was performed with G*Power 3.1.

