### Interim analyses {21b}

An interim analysis will be conducted when the sample size reaches 50 participants. Employing the alpha-spending function, which is a commonly used method for interim analysis in clinical trials, the alpha level was determined to be 0.00305 for the interim analysis and 0.04695 for the final analysis of the primary outcome. The alpha level for the secondary outcomes in the final analysis will be adjusted to 0.00783 using the Bonferroni correction. Also, the sociodemographic data of the participants that were included in the interim analysis will be compared with the total sample using a multivariate ANOVA with the factor participant group (interim analysis vs. remaining participants). The study will be terminated in the event of severe adverse effects that demonstrate noticeable or statistically significant declines in the primary and secondary outcomes.

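### The secondary alpha of 0.00783 covers six tests, but the outcomes as scored give 14 or 15 between-group scores, and no single HLQ-G score is defined

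*Protocol article*

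**What the plan says.** Interim analyses {21b} splits the overall alpha: "the alpha level was determined to be 0.00305 for the interim analysis and 0.04695 for the final analysis of the primary outcome". It then sets the level for everything below the primary outcome: "The alpha level for the secondary outcomes in the final analysis will be adjusted to 0.00783 using the Bonferroni correction". It gives neither the divisor nor a list of the tests to which the level applies.

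Outcomes {12} describes how each secondary questionnaire is scored:

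- HEALTH-49: "the two modules Psychological Well-Being (5 questions) and Self-Efficacy (5 questions) of the HEALTH-49 were selected". That is two scores.
- HADS-D: "recorded on two Likert-type subscales with seven items each that range from zero to three". That is two scores. A sum of the two is also described, as a measure of general impairment.
- CFQ-D: one total score.
- HLQ-G: "The questionnaire comprises 44 questions distributed across nine domains". On scoring, "To obtain scores for each domain, the response to the questions are summed and averaged". That is nine scores. No total is described, and the response range is 1 to 4 for the first five domains and 1 to 5 for the other four.

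The Abstract lists these four instruments as secondary outcomes and leaves the list open. Objectives {7} includes health-related competence in the first secondary research question. Outcomes {12} says that the HLQ-G is meant both as a control variable and as a way of detecting a benefit of the intervention.

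**The concern.** A Bonferroni level protects a family only if the divisor is the number of tests run at that level. Here the level is fixed as a number in one section and the scores are fixed in another, and the two do not match unless the nine HLQ-G domains somehow become one test.

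What is at stake is the reading of the secondary results. If every domain is tested at 0.00783, a report could call a single HLQ-G domain Bonferroni-significant although the correction never allowed for nine looks at that questionnaire. Picking one domain as the HLQ-G test after the data are seen would be no better. Neither fault can be repaired credibly once results are known.

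**Working it through.** **Inputs.** From Interim analyses {21b}: final alpha 0.04695, secondary level 0.00783. From Outcomes {12}: 2 HEALTH-49, 2 HADS-D (plus a possible cumulative score), 1 CFQ-D and 9 HLQ-G scores. Left out of the count: the System Usability Scale, which only the intervention group completes, and the additional post-COVID measures at the Jena site, whose analysis is labelled exploratory in Methods for additional analyses {20b}.

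**Step 1: reproduce the plan's figure.** The implied divisor is 0.04695 / 0.00783 = 5.996, so six, and 0.04695 / 6 = 0.007825, which rounds to 0.00783. Starting from 0.05 does not reproduce it: 0.05 / 6 = 0.00833 and 0.05 / 7 = 0.00714. With 0.04695 as numerator, five gives 0.00939 and seven gives 0.00671. Only 0.04695 / 6 fits.

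**Step 2: count the scores.** 2 + 2 + 1 + 9 = 14, or 15 with the HADS-D cumulative score. Six requires 2 + 2 + 1 + 1, with HLQ-G as one test.

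**Step 3: family-wise error at 0.00783 per test.** The bound is k × 0.00783. Under independence it is 1 − (1 − 0.00783)^k.

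| Tests k | Bound | Independent |
|---|---|---|
| 6 | 0.0470 | 0.0461 |
| 14 | 0.1096 | 0.1042 |
| 15 | 0.1175 | 0.1112 |

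For 14 tests, the bound is 0.1096 / 0.04695 = 2.3 times the implied level.

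**Step 4: allow for correlation.** The document gives no correlations between the scores, so the values here are assumptions. Two-sided z-tests with all null hypotheses true were simulated (400,000 draws). Two-sided testing is itself assumed: the document states "two tails significance level" for the sample size and says nothing separate for the secondary outcomes.

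| Assumed common correlation | 6 tests | 14 tests | 15 tests |
|---|---|---|---|
| 0.2 | 0.045 | 0.099 | 0.105 |
| 0.3 | 0.044 | 0.092 | 0.098 |
| 0.5 | 0.039 | 0.075 | 0.079 |
| 0.7 | 0.031 | 0.053 | 0.055 |

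Letting the HLQ-G domains correlate at 0.4 to 0.7 with each other, the other scores at 0.4 to 0.5, and the two blocks at 0.1 to 0.3, gives 0.071 to 0.092 for 14 tests. Every value tried for 14 or 15 tests is above 0.047.

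**Step 5: matching levels.** 0.04695 / 14 = 0.00335; 0.04695 / 15 = 0.00313.

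**The case against.** The strongest reply is that six is a sensible count of constructs: well-being, self-efficacy, depression, anxiety, everyday cognitive failures and health literacy. Objectives {7} treats health-related competence as one item, not nine. The document says how HLQ-G domains are scored, but nowhere says that each will receive a confirmatory test at 0.00783. A list of tests is commonly left to the analysis plan, which is not shown.

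Much of this stands, and it rules out three stronger readings that a reader might infer.

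- That 0.00783 is a miscalculation. It is not; the division is right for six tests. The point is the match between the level and the outcomes.
- That the plan commits itself to 14 confirmatory tests and so runs at double its error rate. The 14 is a count of scores, and testing all of them is an inference. Roughly double is the bound, the independent case or weak correlation; with strongly correlated scores the excess is small. The 0.047 target is likewise inferred, from the Bonferroni label and the divisor.
- That effects on cognitive domains, mentioned as an aim at the end of Background and rationale {6a}, are further uncovered tests. They are not among the secondary outcomes named in the Abstract or the secondary questions in Objectives {7}, and the Abstract's list is open, so the document cannot settle it.

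What the reply does not remove is the gap itself. Counting health literacy as one construct does not supply one score to test: only domain scores are described, and their unequal response ranges mean that a total would need a rule. No HLQ-G domain is labelled exploratory, although that label is used for the subgroups and the post-COVID outcomes. The HLQ-G's role as a control variable does not take it out of the family either, since it is also named as an outcome.

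**Conclusion.** The point holds as a multiplicity and consistency matter that should be fixed. The level covers six tests, and the described scoring yields 14 or 15 scores. The two agree only through a single HLQ-G test that is not defined.

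The size is conditional on all 14 scores being tested at the stated level. The error would then lie between about 0.05 and 0.11, depending on correlations that the document does not give. The divisor of six is firm, being the only one that reproduces the figure; the count of confirmatory tests is not.

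The primary outcome, its alpha and its power are untouched. The consequence is confined to secondary claims, mainly those on health literacy.

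**What to change.** Before the final analysis, do one of the following:

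1. Keep 0.00783 and list the six confirmatory tests by name: the two HEALTH-49 modules, the two HADS-D subscales, the CFQ-D total, and one HLQ-G score or domain specified in advance. Label the remaining HLQ-G domains, and the HADS-D cumulative score if it is analysed, as exploratory.
2. Test all the scores and set the divisor to their number: 0.00335 for 14, or 0.00313 with the HADS-D cumulative score.

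Under either option, Holm's procedure may replace Bonferroni. It holds the same family-wise error and is never less powerful, but this is an optional gain: Bonferroni is valid once the family is named.

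The change is wording only and needs no new data. Option 1 costs confirmatory claims on eight of the nine HLQ-G domains if a single domain is chosen. Option 2 costs power on every secondary test, because the per-test level falls to less than half of 0.00783.

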**Methods:**

This study protocol presents a single-blinded multicenter randomized controlled trial that will be carried out in six study centers in Germany and Luxembourg. We included adults with MCI (existing F06.7 ICD-10-GM diagnosis and TICS ≥ 21 and ≤ 32). The intervention group will use a mobile, multi-domain cCT (“NeuroNation MED”) for 12 weeks. Meanwhile, the wait list control group will receive standard medical care or no care. The eligibility of volunteers will be determined through a telephone screening. After completion of the baseline examination, patients will be randomly assigned to one of the experimental conditions in a 2:1 ratio. In total, 286 participants will be included in this study. The primary outcome is the change of cognitive performance measured by the index score of the screening module of the Neuropsychological Assessment Battery. Secondary outcomes are changes in the Cognitive Failures Questionnaire, Hospital Anxiety and Depression Scale, Health-49, Health Literacy Questionnaire, among others. All of the primary and secondary outcomes will be assessed at baseline and after the 12-week post-allocation period. Furthermore, the intervention group will undergo an assessment of the System Usability Scale, and the training data of the NeuroNation MED application will be analyzed.

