## Objectives {7}

The multicenter randomized controlled study aims to investigate the effectiveness of the NeuroNation MED training app on the cognitive abilities of patients with MCI. The intervention group (IG) will utilize the app for a duration of 12 weeks, with a recommended training intensity of three sessions per week, each lasting approximately 25 to 40 min. The wait list control group (CG) can receive their regular conventional medical care prescribed by a physician or no medical care at all, but will not have access to the training app or use any other cCT during the study period.

The primary objective of this study is to determine the effectiveness of the training program in improving the cognitive abilities of individuals with MCI. Additionally, the study aims to investigate the influence of the training program on subjective cognitive functioning, health competence, depressive and anxious symptoms, and psychological well-being. Also, the usability of the provided training program will be evaluated. Furthermore, patient diaries will be utilized to gather comprehensive information regarding additional cognition-oriented lifestyle activities and therapies that are not part of the intervention.

Primary research question:Does a 12-week mobile self-administered cCT program improve cognitive abilities of patients with MCI?H0: There is no significant difference in the index score of the screening module of the Neuropsychological Assessment Battery (S-NAB) between IG and CG.H1: There is a significant difference in the index score of the S-NAB between the IG and CG, favoring the IG.

Secondary research questions:Does the use of the mobile cCT program lead to an improvement in depressive and anxious symptoms, subjective cognitive functioning, psychological well-being, and health-related competence in patients with MCI?Are there associations between the usage of the NeuroNation MED app, sociodemographic data, and changes in cognitive and psychosocial outcomes within the intervention group?How do participants within the IG perceive and evaluate the usability of the NeuroNation MED app?

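### Single-step Bonferroni for the secondary outcomes is valid but needlessly conservative; Holm's procedure at the same family-wise level would detect 0 to about 12 percentage points more true effects

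*Protocol article*

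**What the plan says.** Under Interim analyses {21b}, the article first splits the alpha of the primary outcome between two looks: "the alpha level was determined to be 0.00305 for the interim analysis and 0.04695 for the final analysis of the primary outcome". It then fixes the rule for the secondary outcomes: "The alpha level for the secondary outcomes in the final analysis will be adjusted to 0.00783 using the Bonferroni correction". It mentions no step-down, hierarchical or gatekeeping procedure. Both the method and the number are therefore stated in the article and not left to an analysis plan that is not shown.

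The secondary outcomes serve a formal research question in Objectives {7}: "Does the use of the mobile cCT program lead to an improvement in depressive and anxious symptoms, subjective cognitive functioning, psychological well-being", followed there by health-related competence. The Abstract lists the instruments with an open end: "Secondary outcomes are changes in the Cognitive Failures Questionnaire, Hospital Anxiety and Depression Scale, Health-49, Health Literacy Questionnaire, among others". The number of tests in the family is not stated.

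**The concern.** Single-step Bonferroni holds every test to the smallest level, even after other hypotheses in the family have been rejected. Holm orders the p-values. It tests the smallest at alpha/k, the next at alpha/(k-1), and so on, and stops at the first failure. It uses the same p-values and needs no assumption about correlation. Its family-wise error has the same bound.

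The authors chose to control error across the secondary outcomes, so this family is meant to support claims about mood, subjective cognition, well-being and health competence. One intervention is expected to act on all of them. If several effects are real, the single-step rule can leave some unconfirmed that Holm would confirm from the same data.

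**Working it through.** **Inputs**
- Family-wise level: 0.04695, from Interim analyses {21b}.
- Group sizes, from Sample size {14}: "if 164 subjects are included in the IG and 82 subjects are included in the control group".
- Effect size, from the same section: "differences with an effect size of 0.39 or greater can be shown". This is the planning effect of the trial. Using it for the questionnaires is an assumption, so 0.20 to 0.50 was also run.
- Number of true effects (1 to 6) and correlation between outcomes (0, 0.3, 0.5, 0.7): not in the article, so assumed as ranges.

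**The plan's own figure**

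0.04695 / 6 = 0.007825, which rounds to 0.00783. No other divisor from 2 to 15 gives it, and 0.05 / 6 = 0.00833 does not. So k = 6.

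**Levels under each rule**
- Bonferroni: 0.007825 for all six tests.
- Holm, from smallest to largest p-value: 0.04695 divided by 6, 5, 4, 3, 2, 1 = 0.00783, 0.00939, 0.01174, 0.01565, 0.02348, 0.04695.

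**Bonferroni power for one outcome at 0.39**
- Standard error of the standardised difference: sqrt(1/164 + 1/82) = 0.1353.
- Expected z: 0.39 / 0.1353 = 2.88.
- Critical z at two-sided 0.007825: 2.66.
- Power: Φ(2.88 − 2.66), which is 0.589 with unrounded values.

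**Holm against Bonferroni by simulation**

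There were 200,000 runs per setting, each with six equally correlated two-sided z-tests. The measure is the mean share of true effects detected. Bonferroni stays at about 58.9% throughout at 0.39. The ranges below cover correlation 0 to 0.7.

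| True effects of six, each 0.39 | Gain from Holm (points) |
|---|---|
| 1 | 0.0 to 0.1 |
| 2 | 1.2 to 1.5 |
| 3 | 2.8 to 3.2 |
| 4 | 4.5 to 5.3 |
| 5 | 6.6 to 8.0 |
| 6 | 9.5 to 11.9 (Holm 68.5% to 70.8%) |

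| All six true, each of size | Gain from Holm (points) |
|---|---|
| 0.20 | 0.9 to 3.1 |
| 0.25 | 2.5 to 5.2 |
| 0.30 | 5.6 to 7.5 |
| 0.35 | 9.1 to 9.7 |
| 0.45 | 8.3 to 12.2 |
| 0.50 | 6.3 to 9.3 |

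With all six true at 0.39 and correlation 0.3 to 0.7, the chance of confirming all six rises from 14–31% to 39–55%.

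**Error control**

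Holm's family-wise error was at or below 0.047 in every setting. With no true effects the two rules have identical family-wise error, because Holm's first step is the Bonferroni test.

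**The case against.** The strongest reply is that nothing here is wrong. Bonferroni is valid under any dependence and is fully pre-specified, and choosing between two valid procedures for secondary outcomes may look like taste. It stands that this is no error and that type I error is unaffected. It does not settle the matter, because as a rejection rule Holm is never worse at the same level.

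A reader might infer that Holm finds about 10 points more of the true effects here without condition. The article does not support that. The figure needs all six effects to be real and roughly 0.35 to 0.45 in size, and the article states no effect size for any questionnaire. Nor does correlation between the outcomes help. At 0.39 with all six true, the gain falls from 11.9 points at correlation 0 to 9.5 at correlation 0.7. What drives it is how many effects are real and how large they are.

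A reader might also infer that Bonferroni has no advantage at all. It has one: intervals at level 1 − 0.00783 match its tests directly. With unadjusted intervals, an outcome could exclude zero and still fail under Holm. Statistical methods {20a} promises confidence intervals but does not commit to Bonferroni-adjusted ones, so no stated plan would be lost.

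The family is also uncertain. Two HEALTH-49 modules, two HADS-D subscales, the CFQ-D and one HLQ-G result would make six. Yet for the HLQ-G "The questionnaire comprises 44 questions distributed across nine domains", and no total score is described. Counting the nine separately gives 5 + 9 = 14 tests and 0.04695 / 14 = 0.00335. The gains above would then differ. Holm's dominance would not, but either rule needs the list of tests.

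Last, the change would come late: Trial status expected the last patient out in November 2023. That bears on how the change is documented, not on its merit.

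**Conclusion.** The point holds as a cheap improvement. The direction is certain: at family-wise level 0.04695, Holm keeps the same protection and never rejects less than the single-step rule. The size is not certain. It runs from nothing to about 12 percentage points of average power per true effect, and the upper end is close to a best case. The figures rest on six tests, 164 against 82 evaluable participants, equal correlation, and effect sizes taken from the primary planning assumption or a range around it. How alpha is shared with the primary outcome, and which tests belong to the family, are separate questions that this point does not settle.

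**What to change.** In Interim analyses {21b}, replace the Bonferroni correction for the secondary outcomes by Holm's step-down procedure at the same family-wise level, applied to an explicit list of the secondary tests. Report Holm-adjusted p-values. Record the change and its date before the secondary comparisons in the final data are seen, because a later move to a less conservative rule would look data-driven.

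The cost is one sentence, one line of code and a documented amendment. No participants are added. The downside is that simultaneous confidence intervals matching Holm are less simple. Intervals would be shown unadjusted and labelled as such, with significance read from the adjusted p-values.
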